### Definition of the intervention

#### Educational workshop

The educational workshop will be received by both IG and CG participants. In both cases, after randomization. This workshop called “Digital Balance: Disconnect to (re)connect” will last approximately 20 min and will address the following contents:

Digital balance: definition, difference between necessary time and time for recreational use in front of the screens.Reflecting on the relationship with technology and new devices.Establish limits: define periods of disconnection and limit the use of social networks.Be aware of the content consumed on networks.Identity and digital footprint on the Internet.

#### Neurofeedback-Assisted Mindfulness Training Program (NAMTP)

The NATMP will be carried out by the IG alone for a period of 3 months after randomization. A total of 25 sessions will be carried out at a frequency of 2–3 per week. Each session will have a duration of 10/15 min. The organization of the sessions is described in Table 1 of this study protocol.

**Table 1 tab1:** Description of the Neurofeedback-Assisted Mindfulness Training Program (NAMTP).

Week	Number of session	Name of the session	Program of the session	Duration
01	01	Mind meditation: A focused attention practice. Your first mind meditation	Discover Mind Biofeedback	05:19
		Intro: Muse breath meditation. Your first breath meditation	Discover Heart, Breath and Body	06:00
01	02	Anchoring attention	Discover Mind Biofeedback	07:08
01	03	Counting breaths	Discover Mind Biofeedback	07:18
02	04	Letting thoughts pass	Discover Mind Biofeedback	06:42
		Fresh Air: 4 s Box Breath	Breath	05:00
02	05	Extending the exhale	Discover Heart, Breath and Body	08:00
03	06	Posture and body positioning	Discover Mind Biofeedback	09:19
03	07	Building the habit	Discover Mind Biofeedback	11:57
04	08	Training a puppy	Muse Essentials	10:00
04	09	Sensation of breath	Muse Essentials	10:00
05	10	Counting breaths	Muse Essentials	10:00
05	11	Sitting comfortably	Muse Essentials	10:00
06	12	Finding your soundscape	Muse Essentials	10:00
06	13	Dealing with distraction	Muse Essentials	10:00
07	14	Working with discomfort	Muse Essentials	10:00
07	15	Lowering the bar	Muse Essentials	10:00
08	16	Finding clarity and playfulness	Muse Essentials	10:00
08	17	Mind Biofeedback meditation (EEG) Unguided	Mind	10–15 min
09	18	Mind Biofeedback meditation (EEG) Unguided	Mind	10–15 min
09	19	Mind Biofeedback meditation (EEG) Unguided	Mind	10–15 min
10	20	Mind Biofeedback meditation (EEG) Unguided	Mind	10–15 min
10	21	Mind Biofeedback meditation (EEG) Unguided	Mind	10–15 min
11	22	Mind Biofeedback meditation (EEG) Unguided	Mind	10–15 min
11	23	Mind Biofeedback meditation (EEG) Unguided	Mind	10–15 min
12	24	Mind Biofeedback meditation (EEG) Unguided	Mind	10–15 min
12	25	Mind Biofeedback meditation (EEG) Unguided	Mind	10–15 min

The instrument to be used for the neurofeedback sessions is MUSE^®^ (InteraXon Inc.), using two models MUSE^®^ 2 Headband and MUSE^®^ S Headband. MUSE^®^ is a multi-sensor headband device that has been tested and validated against EEG systems and provides real-time information on brain activity, pulse and respiration. Figure 2 shows the MUSE^®^ headbands. These headbands use 7 finely calibrated sensors—2 on the forehead, 2 behind the ears plus 3 reference sensors. MUSE^®^ is a state-of-the-art EEG system that uses advanced algorithms to train beginner and intermediate meditators to control their concentration. It teaches users to manipulate their brain states and change the characteristics of their brain. Unlike traditional neurofeedback (which focuses on training individual frequencies), the MUSE^®^ app goes further and incorporates a unique and complex combination of various brainwaves to deliver results such as calm, active and neutral states.

**Figure 2 fig2:**
[figure not shown]
MUSE^®^ 2 and MUSE^®^ S Headbands (InteraXon Inc.).

Both models, MUSE^®^ 2 Headband and MUSE^®^ S Headband, record EEG signals at a sampling rate of 256 Hz, which are transferred via a Bluetooth connection with the MUSE^®^: EEG Meditation & Sleep mobile app. The MUSE^®^ app transforms and processes brain signals using Machine Learning techniques into information that it returns to the individual for personalized NF-based training. Read more: https://choosemuse.com/.

MUSE^®^ devices and the MUSE^®^: EEG Meditation & Sleep application have been used in clinical studies analyzing anxiety (30) and stress (31), as well as in interventions to manage obsessive compulsive disorders (32) or in the assessment of brain performance (33).

At the beginning of each session, participants completed an initial calibration process in which the device determined the user’s baseline EEG profile over a period of time involving concentration versus distraction. The main proprietary measure of “calm” produced by MUSE^®^ has a sampling frequency of 1 Hz. It is a measure of momentary attention to breathing, with a range of 0–100. MUSE^®^ also produces a measure of “recoveries” for each session, i.e., the number of times the user refocuses on calm breathing after an episode of mental wandering. A third measure, “birds,” represents moments of sustained attention for longer than 5 s. At the end of each session, a registration form should be completed following the model shown in Table 2.

**Table 2 tab2:** Record form for each session.

Number of the session:	Name of the session:		Type of session: □ Guided □ Non-Guided
Data:		Duration:	
MIND			
% Calm:	Active mind time:	Neutral mind time:	Calm mind time:
STILLNESS			
% Still:	Active time:		Relaxed time:
HEART RATE			
Average Heart rate:	High Heart rate:		Low Heart rate:
BREATHING			
% High harmony:	Time low harmony:	Time media harmony:	Time high harmony:
No recoveries:		No birds:	
*How did you feel during the session?* 			

### Data analysis

Variables will be collected in a database in the SPSS v.28 statistical package. An intention-to-treat analysis will be performed, so that the results of all individuals entering the study will be analyzed, regardless of whether or not they complete the study protocol. This will allow us to assess the effect according to the percentage of adherence to the sessions, as well as to avoid biased calculations by including all participants. The normality of the variables collected will be evaluated using the Kolmogorov–Smirnov test (34). The characteristics of the sample will be expressed by frequency distribution and percentages for categorical variables; and calculation of mean and standard deviation for quantitative variables. In the case of parametric distributions, the association between variables will be analyzed with Student’s *t*-test and analysis of variance (ANOVA). In the case of not following a normal distribution, the corresponding nonparametric tests of the previously mentioned tests will be used. The Student’s *t*-test (Mann Whitney U) for independent samples will be used to compare the means between two groups, evaluating the change within the same group with the Student’s *t*-test for paired data (Wilcoxon test). The relationship between quantitative variables will be analyzed using Pearson’s correlation coefficient or Spearman’s correlation coefficient for non-normal variables. A repeated measures analysis (a between-groups repeated measures ANOVA) will be performed as well as an estimation of the parameters and the effect size. For the bilateral contrasts of hypotheses an alpha risk of 0.05 is set as the limit of statistical significance.

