### Sample size calculation

The sample size estimation is based on the expected results in one of the main variables, which is the change in anxiety symptoms. This estimate was made using the results collected in the study by Abdian et al. (21), who conducted a study similar to the one we propose using the DASS-21 anxiety scale score as a change variable, obtaining a mean difference between groups after the intervention of 3.9 points in this questionnaire. Accepting an alpha risk of 0.05 and a beta risk of 0.2 in a bilateral contrast, 40 participants (20 participants in the experimental/intervention group and 20 in the control group) are required to detect a clinically relevant difference equal to or greater than 3.9 points on the DASS-21 anxiety questionnaire. The statistical power of a hypothesis test is 93% to detect the difference between the means as statistically significant. The common standard deviation on this questionnaire, according to data provided by Abdian et al. (21) is assumed to be 3.7. A loss to follow-up rate of 30% has been estimated.

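### The plan promises to analyse everyone who enters, but the effect tests it names can use only participants with a 3-month value

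*Protocol article*

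**What the plan says.** All of the following is in the protocol article.

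- **Analysis set (Data analysis).** "An intention-to-treat analysis will be performed, so that the results of all individuals entering the study will be analyzed". The section adds that this holds whether or not a participant completes the protocol, and that including everyone guards against bias.
- **Methods (same section).** It names independent and paired t-tests, Mann-Whitney and Wilcoxon as their nonparametric counterparts, and ANOVA. It then says: "A repeated measures analysis (a between-groups repeated measures ANOVA) will be performed".
- **Adherence (same section).** Directly after the intention-to-treat statement: "This will allow us to assess the effect according to the percentage of adherence to the sessions".
- **Expected loss (Sample size calculation).** "A loss to follow-up rate of 30% has been estimated".
- **Measurement times (Study variables).** There are two: baseline and 3 months after randomisation.
- **Final visit (Inclusion, randomization and procedures).** A final evaluation is intended for every participant.

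**The concern.** The section claims a property (everyone is analysed) and a benefit from it (less bias), then names methods that do not have that property when final values are missing. With one post-randomisation measurement, a participant without it contributes nothing to a t-test on final scores, to a paired test, or to the group-by-time test of a repeated-measures ANOVA. The published result could then carry an intention-to-treat label while being a complete-case comparison, open to selection by dropout.

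The final-score and change-score comparisons are also named without ranking, and the same dropout can push them in opposite directions.

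The adherence sentence raises a related problem. It presents an effect by adherence as something that intention-to-treat provides. Intention-to-treat compares arms as randomised, whatever the adherence. Only the intervention group has sessions, so controls have no adherence percentage.

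**Working it through.** **Inputs from the Sample size calculation section.** Error rates: "Accepting an alpha risk of 0.05 and a beta risk of 0.2 in a bilateral contrast". Difference: 3.9 points on DASS-21 anxiety. Common SD: "is assumed to be 3.7". Size: "40 participants (20 participants in the experimental/intervention group and 20 in the control group) are required". Stated power: 93%. Loss: 30%.

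**1. The plan's own figures.**
- n per arm = 2 × (1.96 + 0.842)² × (3.7/3.9)² = 14.1, rounded up to 15.
- 15 × 1.3 = 19.5, rounded up to 20 per arm, or 40 in total. The stated size is therefore reproduced if it already includes the 30% allowance by this multiplication. Dividing by 0.7 instead gives 15/0.7 = 21.4, or 22 per arm.
- Power with 20 per arm: 3.9 / (3.7 × √(2/20)) = 3.33. This gives 91.5% by the normal approximation and 90.1% by the noncentral t, close to the stated 93%. That power therefore refers to 40 observed participants.

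**2. What the named methods can use.** With two visits, the group-by-time F test of the repeated-measures ANOVA is the square of the t-test on change scores, so both values are needed. The paired t-test and Wilcoxon test also need both. The independent t-test and Mann-Whitney test on final scores need the final one.

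**3. Size of the gap at the planned loss.**
- 0.30 × 40 = 12 without a final value; 28 remain, or 14 per arm if loss is equal.
- 3.9 / (3.7 × √(2/14)) = 2.79. Power is 76.6% by the noncentral t (79.6% by the normal approximation), against 90.1% (91.5%) with 20 per arm.

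**4. How much bias could follow (illustration on assumed inputs).** The assumptions, none of them in the documents, are: baseline and final scores bivariate normal with SD 3.7 and correlation r = 0.5; 30% loss in each arm; loss in the intervention arm following a logistic model in baseline score; loss in controls random. If m is the shift in mean baseline among intervention-arm completers, the final-score difference shifts by r × m, the change-score difference by (r − 1) × m, and the baseline-adjusted difference by r × m − r × m = 0. By simulation, in points:

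| Odds ratio of loss per SD | m | Final-score bias | Change-score bias | Baseline-adjusted bias |
|---|---|---|---|---|
| 1.65 | −0.53 | −0.26 | +0.26 | about 0 |
| 2.7 | −0.93 | −0.47 | +0.46 | about 0 |
| 4.5 | −1.21 | −0.60 | +0.61 | about 0 |

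Against the 3.9-point target this is 0.26/3.9 = 7% to 0.61/3.9 = 16%. If loss depends on baseline in the same way in both arms, m is the same in each and the between-group bias is zero.

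**5. Adherence.** The section describing the training programme gives the 25 sessions to the intervention group alone. A comparison by percentage of sessions attended therefore has no randomised counterpart among controls.

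**The case against.** The strongest reply is that no sentence says participants are dropped. Deletion is inferred from the methods, and an imputation rule followed by the named tests would satisfy both statements. Such a rule may sit in a full protocol or SAP that is not shown, and its absence from an article is no finding. That stands as far as it goes: the point is not the missing rule. It is that the article claims full inclusion and a benefit from it, and the methods as described do not supply either.

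A reader might infer several stronger things that the documents do not support:

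- **That 12 participants will be excluded.** Twelve is a planning expectation, and the sample size appears to allow for it already.
- **That the protection of intention-to-treat is lost altogether.** A final evaluation is planned for everyone. People who stop the sessions but attend at 3 months are analysed in their randomised arm, so protection against non-adherence remains.
- **That the result will be biased.** This needs loss that depends on prognosis and differs by arm. Twenty-five sessions against a 20-minute workshop, without participant blinding, makes that plausible. But the plan gives one overall loss rate and schedules session reminders, and nothing documents a difference. Even the largest illustrated bias, 0.61 points, is about 0.44 of a standard error with 14 per arm (3.7 × √(2/14) = 1.40).
- **That the adherence analysis is meant to be primary or causal.** The sentence can be read as saying that keeping everyone makes a further exploratory look possible. The wording still needs correcting, because intention-to-treat does not itself yield that effect.

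**Conclusion.** The point holds in a limited form. The stated inclusion of everyone does not follow from the named tests for participants without a 3-month value. At the planned 30% loss, about 28 of 40 would be analysed and power would be about 77% instead of 90%; this rests on the plan's difference and SD and on equal loss by arm.

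The possible bias of 0.26 to 0.61 points is an illustration under assumed baseline-dependent loss in one arm only, and it is zero when that loss is the same in both arms. It does matter for the choice of method: under that pattern the two comparisons named in the plan err in opposite directions, while a baseline-adjusted estimate does not. The adherence sentence misdescribes what intention-to-treat provides.

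**What to change.** - **Main between-group analysis.** Replace the t-test and repeated-measures ANOVA in this role with a linear mixed model (REML). Its outcomes are the baseline and 3-month scores of all randomised participants, with terms for visit and visit × group, and a common baseline mean. ANCOVA on baseline after multiple imputation by arm is an acceptable alternative. Both keep every randomised participant in the analysis and adjust for baseline. They rely on loss being explained by the data in the model, and they do not recover the unobserved final values.
- **If the named tests are kept instead.** Describe the analysis as complete-case, in participants with a final visit, and remove the claim that including everyone avoids bias.
- **Adherence.** Take the sentence out of the intention-to-treat statement. Label any breakdown by sessions attended as a separate, exploratory, non-randomised analysis within the intervention group.

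The cost is a few sentences and a little analysis time. The mixed model is available in the SPSS package already chosen, and no visit, measurement or participant is added. The change should be made before outcome data are examined.

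### A Kolmogorov–Smirnov pre-test picks the between-arm test score by score; one baseline-adjusted mean difference fixed for every score would be better (modest improvement)

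*Protocol article*

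**What the plan says.** The Protocol article, Data analysis, sets the rule in steps.

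- The gate: "The normality of the variables collected will be evaluated using the" Kolmogorov–Smirnov test. The text does not say whether it is applied per arm or pooled, to raw scores or to changes, or with the Lilliefors correction.
- The switch: "In the case of not following a normal distribution, the corresponding nonparametric tests of the previously mentioned tests will be used". The tests named before this sentence are Student's t-test and ANOVA.
- The two-arm pair, with the rank test given in brackets as the alternative to the t-test: "Mann Whitney U) for independent samples will be used to compare the means between two groups".
- After the switching sentence, and with no normality condition: "A repeated measures analysis (a between-groups repeated measures ANOVA) will be performed as well as an estimation of the parameters and the effect size". The effect size is not defined.
- Descriptive summaries use "calculation of mean and standard deviation for quantitative variables", whatever the normality result.

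Under Sample size calculation, the trial is sized on a cited study of DASS-21 anxiety, "obtaining a mean difference between groups after the intervention of 3.9 points in this questionnaire", with SD 3.7, 20 per arm and 30% loss. Study variables lists five questionnaire scores as primary: SAS-SV, NMP-Q and the three DASS-21 subscales.

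**The concern.** This is a stated rule, not detail left to an analysis plan. The data choose the main between-arm test separately for each score, through a test with little power at this sample size. Three things are at stake.

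1. Two primary scores with similar distributions may be analysed by different methods only because one sample happened to fail the pre-test.
2. The sizing target is a difference in means. Mann–Whitney compares ranks and does not estimate that difference, although the text describes it as comparing means.
3. A score that fails the pre-test has two arm comparisons in the plan, a rank test and a parametric repeated-measures model, and nothing says which is primary.

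**Working it through.** **Inputs from Sample size calculation:** difference 3.9, SD 3.7, two-sided alpha 0.05, beta 0.2, 20 per arm, 30% loss. Completers per arm: 20 × 0.7 = 14 (derived, not stated).

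**The plan's own figure.** n per arm = 2(1.960 + 0.842)² × (3.7/3.9)² = 14.1, so 28.3 in total. Allowing for loss, 28.3/0.7 = 40.4, which agrees with the stated 40. Power at 20 per arm is 0.915 by the normal approximation and 0.901 by the exact noncentral t; the article states 93%. Nothing below depends on that gap.

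**How often the pre-test rejects.** The article gives no score distributions, so the shapes are assumptions (2,000 replicates each). The DASS-like score is a rounded gamma with mean 5 and SD 3.7, limited to 0–21.

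| Shape | Corrected, n = 14 | Corrected, n = 20 | Uncorrected, n = 14 / 20 |
|---|---|---|---|
| Normal | 0.048 | 0.050 | 0.000 / 0.000 |
| Skewness 1 | 0.135 | 0.188 | 0.002 / 0.001 |
| Skewness 1.4 | 0.236 | 0.320 | 0.004 / 0.011 |
| Skewness 2 | 0.414 | 0.576 | 0.017 / 0.036 |
| DASS-like | 0.348 | 0.470 | 0.005 / 0.024 |

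So at 14–20 per group the corrected test misses real skewness in about 42–86% of samples (1 − 0.58 to 1 − 0.14), and the uncorrected test misses it almost always. Applied to a pooled sample of 40, the corrected test rejects the skewed shapes in 0.345–0.902 and the uncorrected test in 0.011–0.223. The unstated details of the gate therefore matter as much as the data. A separate simulation with negative-binomial scores (SD 3.7, means 4 to 6, capped at 21) gave 20–57% corrected and 0.3–3% uncorrected at 14–20, which agrees.

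**What the two-stage rule does to inference.** Each arm is tested with the corrected version, and Mann–Whitney is used if either arm rejects (3,000 replicates; Monte Carlo SE at 0.05 is √(0.05 × 0.95/3000) = 0.004).

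| Data | n per arm | Switch rate (no difference) | Type I, two-stage | Power: t | Power: Mann–Whitney | Power: two-stage |
|---|---|---|---|---|---|---|
| Normal | 14 | 0.096 | 0.055 | 0.769 | 0.730 | 0.765 |
| Normal | 20 | 0.102 | 0.052 | 0.900 | 0.886 | 0.900 |
| Skewed gamma, mean 5 | 14 | 0.446 | 0.049 | 0.766 | 0.835 | 0.821 |
| Skewed gamma, mean 5 | 20 | 0.567 | 0.054 | 0.898 | 0.950 | 0.937 |

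Power is for a 3.9-point shift. Type I error stays within Monte Carlo error of 0.05. Two-stage power is at most 0.835 − 0.821 = 0.014 below the better single test. Even with normal data the rule switches in about 10% of trials.

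**What the adjusted analysis gains.** With baseline–follow-up correlation ρ and equal variances, the variance of the arm difference relative to the unadjusted follow-up comparison is 1 − ρ² for ANCOVA and 2(1 − ρ) for change. With two visits, the group-by-time term of the repeated-measures ANOVA is the change comparison. Since 1 − ρ² ≤ 1 and 2(1 − ρ) − (1 − ρ²) = (1 − ρ)² ≥ 0, ANCOVA is never less precise than either, apart from one degree of freedom.

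**The case against.** The strongest defence is that the switching rule does no measurable harm to error rates, and the simulation supports this. A written rule also limits free choice, and Limitations says those analysing the data will be blinded. The mean difference can still be obtained, because means and SDs are reported regardless and the repeated-measures model comes with parameter estimates. All of this stands and keeps the point modest.

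A reader might go further and infer that a failed normality test leaves no comparison of arms, on the ground that a repeated-measures ANOVA has only within-arm rank counterparts such as Wilcoxon or Friedman. The article does not support that. It names Mann–Whitney for two independent groups. The repeated-measures ANOVA comes after the switching sentence, carries no normality condition, and is not replaced by anything.

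A reader might also infer that a mix of tests across the five primary scores is nearly certain. That depends wholly on assumptions. If a score switches with probability q, independently of the others, the chance of a mix is 1 − q⁵ − (1 − q)⁵. With a per-arm rejection rate of 0.39 (corrected, negative-binomial, mean 5, n = 20), q = 1 − 0.61² = 0.63 and the chance is about 0.89. With uncorrected rates of 0.003–0.03, q is 0.006–0.059 and the chance is about 0.03–0.26. Three of the scores are subscales of one questionnaire, so independence is doubtful, and the article gives no distribution for SAS-SV or NMP-Q.

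Nor does the article tie the effect measure to the pre-test. What stands is narrower: the rank branch itself does not estimate the sized quantity.

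**Conclusion.** The point holds as a modest improvement. The article lets a low-power pre-test, itself not fully specified, choose the between-arm test for each score. It describes a rank test as comparing means, and for non-normal scores it leaves two analyses without naming the primary one. The pre-test detects skewness in roughly 14–58% of samples if corrected and 4% or fewer if not, at 14–20 per group and under the assumed shapes. The cost is an arm comparison and effect measure that are not fixed in advance. It is not inflated type I error or lost power, and it is not the loss of the arm comparison. The figure of 14 per arm assumes that the 30% loss falls equally on both arms and on the 40 recruited.

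**What to change.** Remove the normality gate for the between-arm comparison and replace it with one statement for every score:

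- Compare arms by ANCOVA of the 3-month score, adjusted for the same score at baseline, which is already collected.
- Report the adjusted mean difference with a 95% bootstrap CI, with the bootstrap type and number of resamples fixed in advance. This estimates a difference on the scale used for sizing.
- Keep Mann–Whitney on the change score as a labelled sensitivity analysis for all scores, and no longer describe it as comparing means.
- State that the repeated-measures ANOVA is secondary, or drop it.

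The cost is wording and some bootstrap runs. There may be some power loss against a rank test under heavy skew. In the skewed simulation the unadjusted t-test was below Mann–Whitney by 0.835 − 0.766 = 0.07 at 14 per arm and 0.950 − 0.898 = 0.05 at 20. Baseline adjustment should recover part of this, depending on ρ, which the article does not give; the ANCOVA itself was not simulated.

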### Study variables

Study variables will be collected at the baseline visit and at the final visit (3 months after randomization).

Primary outcomes:

Smartphone addiction: The short version of the Smartphone Addiction Scale (SAS-SV), validated in Spanish by Lopez-Fernandez (23), will be used. This scale consists of 10 items and scores higher than 31 are considered susceptible to the presence of addiction to mobile phones (23). In addition, the age at the beginning of the use of new technologies, age of the first mobile phone, type of devices used to connect to the Internet, hours of daily use of the mobile phone, most frequent activities carried out with the mobile phone (calls and messages, games, entertainment, social networks, Internet search, etc.) will also be collected.Nomophobia: The Nomophobia Questionnaire (NMP-Q) will be used for its evaluation. It is a questionnaire composed of 20 items and validated in Spanish by González-Cabrera (24). The range of scores varies from 20 to 140 points. Scores above 20 would indicate the presence of nomophobia (24).Depression, anxiety and stress: The Spanish version of the Depression, Anxiety and Stress Scale 21-item (DASS-21) was used to assess the presence of negative emotional states (25). This questionnaire consists of 21 items divided into three subscales or categories of 7 items each: depression, anxiety and stress. Each item is scored according to the presence of symptoms during the last week on a four-point Likert scale. The final score is obtained with the sum of the scores for each subscale. The DASS-21 has been used to assess nonclinical samples in different age ranges, including adolescence (26). The presence of adverse mental health symptoms was considered according to the cut-off points proposed by Roman et al. (27) in the validation study with a sample of young people in Spain: DASS-21-Depression≥6 points, DASS-21-Anxiety≥6 points, and DASS-21-Stress≥5 points.

Secondary outcomes:

Sleep quality and signs of insomnia: It will be evaluated through the Athens Insomnia Scale (AIS). This is a tool that helps in the diagnosis and assessment of insomnia according to ICD-10 diagnostic criteria. It consists of 8 items, with four response options scoring from 0 to 3. A higher score on the scale indicates the presence of insomnia symptoms (28).

Other variables:

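### The two planned between-arm tests leave the baseline score unused as a covariate and do not name the treatment term; baseline-adjusted ANCOVA would serve better at no practical cost

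*Protocol article*

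**What the plan says.** On timing, the Study variables section states: "Study variables will be collected at the baseline visit and at the final visit (3 months after randomization". Each score therefore has one value before randomisation and one after.

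The Data analysis section gives three procedures for these scores:

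- **Between arms:** a t-test, or Mann-Whitney U if the variable is not normal, "for independent samples will be used to compare the means between two groups, evaluating the change within the same group" with the paired t-test or Wilcoxon test. The text does not say whether the means compared between arms are final scores or changes.
- **Within each arm:** the paired tests just mentioned.
- **Both together:** "A repeated measures analysis (a between-groups repeated measures ANOVA) will be performed", with parameter estimates and an effect size. The term to be tested is not named.

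No covariate appears in any of these, and none is marked as the analysis that decides.

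The Sample size calculation section treats the trial as a plain comparison of two means on DASS-21 anxiety. It cites an earlier study "obtaining a mean difference between groups after the intervention of 3.9 points in this questionnaire", takes a common SD that "is assumed to be 3.7", and says that "40 participants (20 participants in the experimental/intervention group and 20 in the control group) are required". It also expects 30% loss to follow-up.

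**The concern.** With one baseline and one follow-up value, regressing the follow-up score on arm and baseline has the smallest variance of the usual choices, apart from one degree of freedom. It also removes chance baseline imbalance, which is a practical matter with 40 people. The listed tests give this up.

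The repeated-measures ANOVA raises a second difficulty. In a two-visit design its group main effect averages the pre-randomisation score with the final score, so a true effect is halved. Its group-by-time term is the same test as a t-test on change. These are different tests with very different power, and the text does not choose between them.

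Third, a final-score test and a change-score test answer the same question and can disagree. With no order of precedence, the reader of the results cannot tell which was meant to decide.

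**Working it through.** **Inputs.** From the Sample size calculation section: difference δ = 3.9, SD σ = 3.7, two-sided alpha 0.05, target power 80%, 20 per arm, 30% loss, so 20 × 0.7 = 14 per arm. The correlation r between baseline and 3-month scores is not in the document; I **assume** 0.3, 0.5 and 0.7. I also assume equal SD at both visits, and that the 14 per arm are those with a final score.

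**The plan's own figures.** Normal approximation: n = 2 × (3.7 × (1.960 + 0.842) / 3.9)² = 14.13, so 15 per arm. Multiplying by 1.3 gives 19.5, so 20 per arm and 40 in all, which matches. With 20 per arm, power is 91.5% by the normal approximation and 90.1% by the noncentral t; the protocol states 93%.

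**Power of each analysis.** All use the noncentral t with noncentrality λ = effect / (SD × √(2/n)).

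- Final score: effect δ, SD σ. At n = 14, λ = 3.9 / (3.7 × 0.378) = 2.79.
- Change score, equal to group-by-time: effect δ, SD σ√(2(1−r)).
- ANCOVA: effect δ, SD σ√(1−r²), with 2n−3 degrees of freedom.
- Group main effect: effect δ/2, SD σ√((1+r)/2).

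| Analysis | 14 per arm, r = 0.3 / 0.5 / 0.7 | 20 per arm, r = 0.3 / 0.5 / 0.7 |
|---|---|---|
| Final-score t-test | 77 / 77 / 77% | 90 / 90 / 90% |
| Change score (group-by-time) | 62 / 77 / 93% | 78 / 90 / 99% |
| ANCOVA | 80 / 87 / 96% | 93 / 96 / 99.5% |
| Group main effect | 38 / 34 / 31% | 52 / 47 / 42% |

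**Gain from ANCOVA at 14 per arm.**

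- Over the better unadjusted test: 80.2 − 76.6 = 3.6 points at r = 0.3; 87.2 − 76.6 = 10.6 at 0.5; 96.3 − 93.4 = 2.9 at 0.7.
- Over the weaker one: 80.2 − 62.1 = 18.1 at r = 0.3; 96.3 − 76.6 = 19.7 at 0.7. At r = 0.5 the two unadjusted tests tie.

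The ANCOVA formula ignores the small price of adjusting for chance imbalance. I simulated the full regression with normal scores (40,000 trials per setting, 14 per arm) and got 79/86/96%, so the formula is optimistic by one to two points at most.

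**The same in variance terms, for any score.** ANCOVA variance divided by final-score variance is 1−r²: 0.91, 0.75, 0.51. Divided by change-score variance it is (1+r)/2: 0.65, 0.75, 0.85. Neither ratio depends on 3.9 or 3.7.

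**Two tests of one question.** If either the final-score or the change-score test were counted as success, simulation under no effect at 14 per arm gives about 9% type I error.

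**Paired tests, if misread.** Suppose both arms fall by 2 points (assumed; r = 0.5, 14 per arm) with no arm difference. Each paired test is significant with probability 0.465, so the intervention arm alone is significant with probability 0.465 × 0.535 = 0.25.

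**The case against.** The other side has several good points.

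- **A reader might infer that the trial is short of power.** The documents do not support that for anxiety, the only outcome sized. Their inputs give 90% with full follow-up and 77% after 30% loss, against a target of 80%. The shortfall is small and comes mainly from how loss was allowed for.
- **A reader might infer that baseline is ignored altogether.** It is not. The group-by-time term takes baseline into account by subtraction and is valid in a randomised trial. At r = 0.7 it comes within 3 points of ANCOVA.
- **A reader might take power of about one third as the plan's power.** That needs the group main effect to be the treatment test. The phrase may simply describe a design with group between subjects and time within. The fair statement is that the term is unnamed.
- **A reader might infer that efficacy will be judged from the paired tests.** The text gives them to change within a group and gives the arm comparison to the independent-samples test. The 25% above measures a possible misreading, not a planned inference. Likewise, the 9% needs someone to pick whichever test succeeds, and nothing says anyone will.
- **A condensed article may leave the choice of deciding model to a fuller document.** True, so the lack of a named primary model is not the point by itself. The article does, however, state its tests, and what remains is that those tests are a poor choice for data with a baseline on every outcome.

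**Conclusion.** The point holds in a limited form. The stated between-arm analyses are usable, but ANCOVA has the highest power at each r examined and the article's wording leaves the treatment term open. At 14 per arm the gain is about 4, 11 and 3 points over the better unadjusted test at r = 0.3, 0.5 and 0.7. Which unadjusted test is better depends on an r that the document does not give: choosing wrongly costs up to 18 to 20 points against ANCOVA, and ANCOVA avoids the bet. With all 40 followed up, the gain over the better test is smaller: about 2, 6 and 1 points (92.5 − 90.1, 96.3 − 90.1, 99.5 − 98.7).

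The power figures apply to DASS-21 anxiety and rest on the assumed r, equal SDs and normal scores. For the other scores only the variance ratios carry over. This is an improvement that should be made, not a flaw that invalidates the trial.

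**What to change.** For each score, state one deciding between-arm analysis: linear regression (ANCOVA) of the 3-month score on arm and the same score at baseline, reporting the adjusted mean difference with its 95% confidence interval.

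Drop the repeated-measures ANOVA as a test of effect, or keep only its group-by-time term, named as such and labelled supportive. Report within-arm change descriptively, and say that it is not evidence of efficacy.

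The cost is a few sentences and one degree of freedom. The baseline scores are already being collected, and no extra participants or visits are needed.
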